**Table 10 Causality Assessment Criteria****14.4.1 Seriousness**

The judgement as to whether the adverse event is serious is made by the reporting investigator.

**14.4.2 Outcome**

The outcome of adverse events has to be described by following criteria:

- recovered/resolved
- recovering/resolving
- not recovered/not resolved
- recovered/resolved with sequelae
- ongoing
- fatal
- unknown

Each adverse event has to be followed up:

- until the termination
- until improving is not to be expected
- until database is closed

**14.5 Documentation and reporting of Serious Adverse Events**

All serious adverse events (SAEs) have to be recorded on a study specific SAE form from the time the informed consent has been signed, until end of study (month 15) for arm B plus an additional safety visit for arm A (month 16). After that period of time, only serious adverse reactions (events related to study medication) have to be reported. The SAE form has to be completed in English. The Investigator must fax all serious adverse events (SAEs) **within 24 hours after awareness** of the event to:

KKS Marburg

Philipps-Universität Marburg

[name]

D-35043 Marburg

**FAX-No.: [name]**

The initial SAE report should be carried out by the investigator immediately, even if not all data are available.

**The minimum information of an SAE report should include:**

- Center-No.
- Patient-No.
- Name of reporting investigator
- Medical term of the SAE
- Name of study medication
- Causality assessment (relation between the reported event and the administration of study medication)

Furthermore, it is required for completing the SAE-Report:

- Start date of SAE
- Start date study medication
- Date of last dose (study medication) prior to SAE
- Seriousness criteria
- SAE outcome (at the time of the initial SAE report)
- Severity / Intensity of SAE

Relevant follow-up information must be faxed as soon as possible. SAE-Follow-Up reports also have to be recorded on the study specific SAE pages.

The medical term of the SAE should be an event, reaction or diagnosis rather than a list of symptoms. It is important to enter the most appropriate event term in the corresponding field. **Only one event term/diagnosis** should be entered on each SAE form. If more than one SAE is to be reported for the same patient, a separate SAE form for each SAE has to be completed.

In the case of death of a trial subject, the investigator has to provide any additional information necessary as requested by KKS Marburg (Sponsor), the competent authorities concerned and ethics committees concerned.

#### **14.6 Exceptions from SAE-reporting**

The following hospitalizations are not considered SAEs in this study:

Elective surgery or any other elective medical procedure that was planned prior or after signing consent.

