#### **14.1.4 Serious Adverse Event (SAE) or Serious Adverse Reaction (SAR)**

A serious adverse event or serious adverse reaction is defined as follows:

'Any untoward medical occurrence or effect that at any dose:

- results in death,
- is life-threatening,
- requires hospitalization or prolongation of existing hospitalization,
- results in persistent or significant disability or incapacity,
- or is a congenital anomaly or birth defect'.

'NOTE: The term "life-threatening" in the definition of "serious" refers to an event in which the patient was at risk of death at the time of the event; it does not refer to an event which hypothetically might have caused death if it were more severe'.

The severity of an adverse reaction is largely determined by the outcome of the medical occurrence. An adverse reaction should only be termed "serious" if hospitalization did in fact take place as a result of it. As a rule, hospitalization is the admission to a hospital with at least one overnight stay.

The presentation of a patient in the emergency room (casualty center, health care center) alone without subsequent in-patient admission does not yet fulfill the criterion hospitalization. However, it should be proofed whether any of the other criteria mentioned above justifies an adverse reaction being classified as "serious" or at least "medically significant".

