#### **14.1.5 Suspected Unexpected Serious Adverse Reaction (SUSAR)**

A SUSAR is an adverse event which

- has a reasonable possibility of a causal relationship to an IMP,
- is serious; and

 European Parliament and the Council, 2001: Directive 2001/20/EC. Article 2 (n).

 European Commission, 2011: Detailed guidance on the collection, verification and presentation of adverse event/reaction reports arising from clinical trials on medicinal products for human use ('CT-3'). Section 7.2.1, No. 45

 European Parliament and the Council, 2001: Directive 2001/20/EC. Article 2 (p).

 European Parliament and the Council, 2001: Directive 2001/20/EC. Article 2 (o).

 International Conference of Harmonisation, 2001: ICH Harmonised Tripartite Guideline Clinical Safety Data Management: Definitions and standards for expedited reporting - E2A: Section 2 B.

 Cf. Bundesinstitut für Arzneimittel und Medizinprodukte (BfArM) und Paul-Ehrlich-Institut und Bundesinstitut für Impfstoffe und biomedizinische Arzneimittel, 2010: 6. Bekanntmachung zur Anzeige von Nebenwirkungen und Arzneimittelmisbrauch nach § 63b Absatz 1 bis 9 des Arzneimittelgesetzes (AMG) vom 19.1.2010. Page 8.

 Cf. Bundesinstitut für Arzneimittel und Medizinprodukte (BfArM) und Paul-Ehrlich-Institut und Bundesinstitut für Impfstoffe und biomedizinische Arzneimittel, 2010: 6. Bekanntmachung zur Anzeige von Nebenwirkungen und Arzneimittelmisbrauch nach § 63b Absatz 1 bis 9 des Arzneimittelgesetzes (AMG) vom 19.1.2010. Page 8.

- is unexpected.

Therefore a SUSAR is not consistent with the applicable product information (e.g. Investigator's Brochure (IB) for an unauthorized investigational medicinal product or Summary of Product Characteristics (SmPC) for an authorized medicinal product.

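### The SAE exemption in section 14.6 covers every elective admission, whenever planned, so an elective admission for a condition that is new or worse since consent is not an SAE if no other seriousness criterion is met

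*Protocol*

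**What the plan says.** Section 14.1.4 makes an untoward occurrence serious if, among other criteria, it "requires hospitalization or prolongation of existing hospitalization". It explains the term: "As a rule, hospitalization is the admission to a hospital with at least one overnight stay". Neither sentence separates elective from unplanned admissions.

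Section 14.5 sets the reporting duty: "All serious adverse events (SAEs) have to be recorded on a study specific SAE form from the time the informed consent has been signed", up to month 15 in arm B and month 16 in arm A, with a fax within 24 hours of awareness. After that, "only serious adverse reactions (events related to study medication) have to be reported".

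Section 14.6 then makes the exception. "The following hospitalizations are not considered SAEs in this study", it says, and gives one item: "Elective surgery or any other elective medical procedure that was planned prior or after signing consent".

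Section 14.1.5 requires three things of a SUSAR: that it "has a reasonable possibility of a causal relationship to an IMP", that it "is serious; and" that it is unexpected. Under section 14.7, expectedness is judged against the Investigator's Brochure.

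**The concern.** An exception for procedures already planned at consent has a clear purpose. The condition was there before the trial, so the admission says nothing about the treatment. Once the exception also takes in procedures planned after consent, that reasoning no longer applies. An admission arranged during the trial may be for something that began or worsened on study treatment, and this is what SAE reporting is meant to capture.

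Three things are at stake: the 24-hour report to the sponsor's safety office, the SAE incidence listed among the secondary endpoints in section 4.2, and, for related events not described in the brochure, the SUSAR route in section 14.12.

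**Working it through.** The protocol states no figure on this point and no arithmetic applies. The check is to read the sections against each other.

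**Step 1: what the timing words exclude.** A procedure is planned either before or after consent is signed. The exception names both, so every elective procedure qualifies. Section 14.6 adds no condition that the illness be pre-existing or unchanged, and makes no exclusion for events judged related to AOP2014.

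**Step 2: how different admissions are classified.** Each row assumes at least one overnight stay.

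| Admission during the trial | 14.1.4 alone | With 14.6 |
|---|---|---|
| Unplanned, new condition | SAE | SAE |
| Elective, new condition that is also life-threatening or disabling | SAE | SAE, on the other criterion |
| Elective, planned before consent, pre-existing condition unchanged | Nothing new since consent | Not an SAE, as intended |
| Elective, planned after consent, pre-existing condition worsened | SAE | Not an SAE |
| Elective, planned after consent, new condition | SAE | Not an SAE |

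Only the last two rows are a problem.

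**Step 3: what follows for those two rows.** Under section 14.5 no SAE form is due, because the event is not an SAE. It therefore does not count toward SAE incidence in section 4.2. It also fails the seriousness condition in section 14.1.5, so it cannot become a SUSAR, even when related and absent from the brochure.

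**Step 4: whether another section brings these events back.**
- Section 14.4.1 leaves seriousness to the investigator, but 14.6 has already settled the answer for this class.
- Section 14.11 lists no adverse events of special interest, so there is no separate expedited route.
- The list of criteria in 14.1.4 has no item for medically important events. Medical significance appears only in the paragraph on emergency-room visits.
- Section 14.2 keeps the underlying condition on the case report form as an adverse event, but only to month 15 (arm B) or month 16 (arm A). After that, the one remaining duty in 14.5 again depends on the event being serious.

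No other section of the protocol narrows 14.6.

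**The case against.** The strongest reply is that 14.6 is headed as a list of exceptions. An express exception to a general rule is not a contradiction of it, and what 14.6 declares not to be an SAE falls outside 14.5. That stands. A reader might infer that 14.6 flatly contradicts 14.1.4 and 14.5, but the fair criticism is that the exception is wider than its purpose needs.

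Other stronger readings are tempting and are not supported:

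- *That hospital admissions for new problems on AOP2014 drop out in general.* Only elective admissions do, and only where hospitalization is the sole seriousness criterion.
- *That the events vanish from the safety data.* During the collection window the condition is still recorded, graded, assessed for causality and followed to outcome (sections 14.2 to 14.4.2). It enters the adverse-event analyses in sections 16.6 and 16.7, and the monitoring committee may review adverse events in both arms (section 17.2). What is lost is expedited reporting and the SAE count.
- *That conditions listed in section 10.2, such as atrial fibrillation or Basedow's disease, would be lost SUSARs.* That list reproduces the brochure's table, so these are ordinarily expected. They can illustrate a missing SAE report, but not a missing SUSAR.
- *That the SAE comparison is biased toward no harm.* The rule applies to both arms. Any understatement of the difference depends on how many such admissions AOP2014 causes, which the documents do not tell us.
- *That a count of missed patients can be given.* Section 2.3.2 reports SAEs in 9 of 34 polycythemia vera patients, and scaling that to 214 / 2 = 107 arm A patients gives 107 × 9/34 ≈ 28. But those SAEs were of any cause, with only 4 considered treatment related. The mean dose was 287 µg, against a maintenance dose of 100 µg here, and the disease was different. The share that was serious only through an elective admission is not stated anywhere.

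Finally, section 14.13 leaves detailed procedures to a Safety Manual that is not at hand. It may narrow the rule in practice, so how sites will apply 14.6 cannot be known from the protocol. The protocol text should still not depend on it.

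**Conclusion.** The point holds for a defined class: elective overnight admissions arranged after consent, for a condition that is new or worse since consent, with no other seriousness criterion met. For these, section 14.6 as written removes the SAE report and the SAE count. Where the event is related and not described in the brochure, it also removes SUSAR assessment.

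The conclusion rests on reading 14.6 literally and on no unseen document narrowing it. It needs no assumption about event rates. The number of events affected cannot be estimated from the documents and may be small. The efficacy hypotheses and the sample size are untouched. The correction is worth making because the rule gives the wrong classification for events that safety reporting exists to catch, and it is cheap to put right.

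**What to change.** In section 14.6, delete the words *or after*. Limit the exemption to hospitalization for an elective procedure that was planned before consent, for a pre-existing condition that has not worsened since consent.

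Add one sentence: an elective admission for a condition that arose or worsened after consent is reported as an SAE, with that condition, and not the procedure, as the event term. Bring the Safety Manual into line.

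The cost is a protocol wording change, the matching edit to the manual and a few more SAE forms. Treatment, visits and the efficacy analysis do not change.

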#### **14.7 Expectedness for IMP (Arm A)**

KKS Safety management determines the expectedness of an adverse reaction according to the actual version of the Investigator's Brochure (IB).

- Expected event: already described in the ☐ SmPC ☒ IB
- Unexpected event: not described in the ☐ SmPC ☒ IB

#### **14.8 Expectedness for Non-IMP**

Not applicable.

#### **14.9 Clinical assessment of relatedness for Non-IMP (both Arms)**

The investigator will also evaluate the Non-IMP-relatedness after discontinuation of the medication.

 European Commission, 2011: Detailed guidance on the collection, verification and presentation of adverse event/reaction reports arising from clinical trials on medicinal products for human use ('CT-3'). Section 7.2.3.2, No. 51, 52.

## 14.10 Pregnancy

Pregnancies must be reported and followed up analogous to a SAE-report. In general, pregnant women should be excluded from clinical trials where the drug is not intended for use in pregnancy. If a patient becomes pregnant during administration of the drug, treatment should generally be discontinued if this can be done safely. It is the responsibility of the investigator to inform KKS pharmacovigilance **within 24 hours after awareness** of the pregnancy by using the study specific pregnancy reporting form (blank form is filed in ISF). Follow-up evaluation of the pregnancy, fetus, and child is very important and has to be reported on the study specific pregnancy reporting form. The pregnancy reporting form, follow-up evaluation and the pregnancy outcome report have to be stored in the ISF.

## 14.11 Adverse events of special interest

- none

## 14.12 SUSAR reporting procedure

According to national legislation and European directives and guidelines, KKS Marburg (Sponsor) of the clinical trial has to report all SUSARs to the competent authority and ethic Committee in all Member States concerned and to the European clinical trials database (Eudravigilance Clinical Trial Module - EVTCM).

'The Sponsor shall ensure that all relevant information about suspected serious unexpected adverse reactions that are fatal or life-threatening is recorded and reported as soon as possible to the competent authorities in all the Member States concerned, and to the Ethics Committee, and in any case no later than seven days after knowledge by the Sponsor of such a case, and that relevant follow-up information is subsequently communicated within an additional eight days'.

'All other suspected serious unexpected adverse reactions shall be reported to the competent authorities concerned and to the Ethics Committee concerned as soon as possible but within a maximum of 15 days of first knowledge by the Sponsor'.

Furthermore it is the Sponsor's responsibility to inform all investigators.

## 14.13 Safety-Manual

KKS Safety management performs the process of SAE-Assessment. In this context a study specific Safety-Manual has to be prepared. The Safety-Manual contains a detailed description of all procedures concerning the documentation and reporting of AEs, SAEs and SUSARs. Additionally the Safety Manual describes the preparation of the Development Safety Update Report (DSUR), the Benefit-Risk-Assessment and the process of immediate actions to prevent the trial subjects from immediate risks.

 European Medicines Agency, 2006: ICH Topic E8. General Considerations for Clinical Trials. Step 5, Section 3.1.4.3 a).

 European Commission, 2011: Detailed guidance on the collection, verification and presentation of adverse event/reaction reports arising from clinical trials on medicinal products for human use ('CT-3'). Section 7.1, No. 37.

 European Commission, 2011: Detailed guidance on the collection, verification and presentation of adverse event/reaction reports arising from clinical trials on medicinal products for human use ('CT-3'). Section 7.1, No. 37.

 See European Commission, 2011: Detailed guidance on the collection, verification and presentation of adverse event/reaction reports arising from clinical trials on medicinal products for human use ('CT-3'). Section 7.10, No. 108.

 See European Commission, 2011: Detailed guidance on the collection, verification and presentation of adverse event/reaction reports arising from clinical trials on medicinal products for human use ('CT-3'). Section 8, No. 124.

 See Bundesministerium für Justiz, 2012: GCP-Verordnung, § 11, §13 (4), §13 (5), §13 (6).

## 15 Data Management

### 15.1 EDC-System (e-CRF) and Data Management

The study will use an electronic case report form (e-CRF/EDC-System) for data collection and documentation, which is hosted by KKS Marburg. The data are entered directly via web browser to the e-CRF and are transferred via encryption (HTTPS (TSL/SSL)) to the central database.

Access to the e-CRF is only allowed for persons who are documented as trial personnel. Each person who is allowed to make entries in the e-CRF receives a personal username and the URL for database login upon request (User-ID request). The initial password, which has to be changed at first login, is transmitted automatically by email to the user upon request (Forgot Password?) to the personal email address, which is recorded in the system.

Before a user gets access to the productive environment, the user account is only activated for training. After the user has activated its account the user management at KKS enables the user for the appropriate site. The access level in the e-CRF depends on the group membership (investigator, study nurse, monitor, etc.). Thus, it is ensured that only authorized persons have access to the EDC system in order to document or monitor patient data. Users with monitoring function are not able to enter or change patient's data. They have the possibility to view the data write protected (review function) and they can use additional review functionality in case of any implausibility or questions/queries.

The completed e-CRF must be electronically signed (authorization) at the end of each visit by an investigator for each patient.

In order to ensure the anonymity of the patient data, the patient data in the e-CRF are recorded with a patient number consisting of a center number and a consecutive number. An allocation list (e.g. Rando-Log) containing the patient's patient number and the identifying data of the patient is only kept in the center.

Users of the EDC system receive training material (EDC Manual), which is provided by the KKS. Furthermore, on the homepage of the KKS Marburg under the heading Online Services (<https://www.kks.uni-marburg.de/index.php/online-services>) the prerequisites for using the system and further notes (FAQ). The EDC-Manual is part of the ISF and contains detailed instructions for using the EDC system. If necessary KKS Marburg will provide additional training material and required documentation for the users. For training purpose of data entry and data review a training site is included in the database.

In a multistage procedure, the given data will be checked electronically for their plausibility and consistency. Even during data collection, implausible data will be flagged automatically by implemented validation checks. Detected inconsistencies and missing or implausible data will be clarified with queries (electronically or paper-based) and necessary changes will be carried out.

The EDC system has an implemented audit trail. This assures that any documentation and/or changes to database items are traceable anytime.

At the end of study, the database will be closed after data cleaning process. This process will be documented according to SOPs of KKS Marburg.

The pseudonymized patient data recorded in the e-CRF are stored by the KKS Marburg in accordance with legal requirements.

## 16 Statistical Considerations

### 16.1 Hypotheses

Four hypotheses are tested in hierarchical order. To avoid inflation of type 1 error (false rejection of a null hypothesis), further confirmatory testing has to be stopped as soon as a null hypothesis could not be rejected. All four hypotheses are tested at significance level 0.05.

At first,

Null hypothesis 1: “The probability of molecular relapse-free survival (RFS) 7 months after randomization / 6 months after stopping TKI is not different between the two arms A and B”

is tested against the

Alternative hypothesis 1: “The probability of molecular RFS 7 months after randomization / 6 months after stopping TKI is different between the two arms A and B”.

In case null hypothesis 1 can be rejected,

Null hypothesis 2: “The probability of molecular RFS 13 months after randomization / 12 months after stopping TKI is not different between the two arms A and B”

is tested against the

Alternative hypothesis 2: “The probability of molecular RFS 13 months after randomization / 12 months after stopping TKI is different between the two arms A and B”.

In case null hypothesis 2 can be rejected,

Null hypothesis 3: “No difference in the molecular RFS probabilities between the two arms A and B at any time”

is tested against the

Alternative hypothesis 3: “Molecular RFS probabilities between the two arms A and B are different”.

In case null hypothesis 3 can be rejected,

Null hypothesis 4: “The probability of molecular RFS 25 months after randomization / 24 months after stopping TKI is not different between the two arms A and B”

is tested against the

Alternative hypothesis 4: “The probability of molecular RFS 25 months after randomization / 24 months after stopping TKI is different between the two arms A and B”.

## 16.2 Analysis Populations

### Definitions of Analysis Populations

|                                     |                                                                                                                                                                                            |
|-------------------------------------|--------------------------------------------------------------------------------------------------------------------------------------------------------------------------------------------|
| Intention-to-treat (ITT) population | All randomized patients                                                                                                                                                                    |
| Safety population                   | All randomized patients who receive at least one dose of treatment in Arm A or attended at Visit 1 in Arm B. The safety population will be used for the analyses of all safety parameters. |
| Per-protocol (PP) population        | All patients in the ITT population for whom no major protocol violations/deviations occurred                                                                                               |

